## **Material and Methods:**

### **Participants & recruitment:**

Out of the total number of hospitalized patients, 48 patients with definitive diagnosis based on PCR test, who also have other inclusion criteria, are included in the study by availability sampling.

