### **Study Design & randomization:**

The present study will be performed as a Randomized, Placebo-Controlled, Double-Blind, Parallel-Group clinical trial on patients with Covid-19 admitted to Shahid Jalil Hospital in Yasuj (Kohgiluyeh & Boyr Ahmad province, south-west of Iran). The study protocol was approved by the Ethics Committee of the School of Nutrition and Public Health ( ) in Yasuj University of Medical Sciences and is in agreement with the declaration of Helsinki of the world medical association. This study was also registered in the Iranian Center for Clinical Trials ( ). Patients will be randomly divided into two groups of intervention (n=24), and placebo (n=24), by block random sampling method, which randomizes participants into 4 different blocks in each group, based on gender and age . Intervention group receive 500 ml of natural whole pomegranate juice twice a day, after lunch and dinner and control group receive the same amount of placebo with the same color and taste as natural juice. The pomegranate juice and placebo will be administered to patients by two nurses in opposite shifts. Patients will be followed for 14 days and the objectives of the study will be fully explained to the patient and their companions. An informed written consent form will be also obtained.

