***Non-inclusion criteria***

- Pregnancy or lactation
- IgA <61 mg/dl
- Disseminated intravascular coagulation or any other types of coagulopathy
- Severe congestive heart failure
- Participate in any clinical trial within the past 30 days prior to enrollment in the present work
- Other contraindications prescribed by the specialist.

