### **Clinical, Para clinical and dietary intake assessments:**

A demographic questionnaire containing information about age, sex, habitat, education, occupation etc., will be taken from patients. Medical history and medications/supplements history will also be asked of the patient or his companion.

Height, weight and waist to hip ratio (WHR) will be measured by standard methods [1] as well as the body mass index (division of weight in kilograms to the height in meters squared).

For the purpose of evaluating detailed information about nutrient intake and the food pattern, a 24-hour dietary recall for 3 days (including a weekend day) will be taken by a well-trained interviewer. Dietary intakes will be entered into Nutritionist IV software for further analysis.

10 cc blood samples will be obtained after 12 hour overnight fasting to measure complete blood count (CBC) and inflammatory indices including CRP, ESR & IL-6, at the baseline and by the end of week-2. In the case of patient discharge earlier than scheduled, they will be followed up after discharge and receive pomegranate juice or placebo. The length of hospital stay, disease complications, drug and prescription dosing and mortality rate will be recorded on a daily basis. If the patient refuses to continue the study for any reason, blood sample will be drawn on the same day.

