### **Follow up:**

Subsequent follow-up is to detect and minimize the effects of the confounding factors, as well as to accurately carry out the intervention protocol and will be done by well-trained, committed researchers.

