## **Data analysis**

The data will be analyzed by SPSS software version 25. After examining the normality distribution of variables using Kolmogorov-Smirnov test, quantitative normal variables will be reported as mean $\pm$ standard deviation, quantitative non-normal variables will be reported as median IQR, and qualitative variables as number (percentage). Independent T Test and Mann Whitney test will be used to compare the mean of variables between two groups. Paired T test or Wilcoxon test will be used to analyses within groups means. P-Value <0.05 will be considered as statistically significant. If the patient refuses to continue the study for any reason, statistical methods (Intention-to-treat analysis) will be performed.

1. STEPS, W., *Section 3: guide to physical measurements (Step 2)*, 2008, Geneva.

[figure not shown]

**Figure 1:** Study Process Flow chart

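### Drug use is recorded and confounding is to be minimised, but the fixed tests take no covariate: precision is lost, and a chance imbalance in anti-inflammatory drugs cannot be separated from a juice effect

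*Protocol*

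**What the plan says.** The primary objective concerns inflammatory biomarkers and CBC. The secondary objectives name IL-6, ESR, CRP and the CBC parameters, each to be compared before and after the intervention and between the groups.

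The section on clinical, paraclinical and dietary assessments asks for medication and supplement history at baseline. During the study, "disease complications, drug and prescription dosing and mortality rate will be recorded on a daily basis". The Follow up section gives a purpose but no method: "Subsequent follow-up is to detect and minimize the effects of the confounding factors".

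On allocation, Study Design & randomization says: "Patients will be randomly divided into two groups of intervention (n=24), and placebo (n=24), by block random sampling method", with blocks formed on gender and age ("which randomizes participants into 4 different blocks in each group, based on gender and age"). The eligibility lists name no restriction on anti-inflammatory treatment.

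The Data analysis section fixes the between-group method: "Independent T Test and Mann Whitney test will be used to compare the mean of variables between two groups". Within groups it uses the paired t or Wilcoxon test. None of these four tests can take a covariate.

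**The concern.** The protocol states an aim (minimise confounding) and collects the data for it (drug history and daily dosing), but the analysis it fixes has no step that uses those data. Because the outcomes are laboratory markers of inflammation, background treatment may move the same quantities that the juice is meant to move.

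Three things are at stake. Variation in drug use that could be explained stays in the error term and lowers power. If the arms happen to differ in drug use, the unadjusted difference mixes drug and juice, and nothing in the stated analysis separates them. The before-after tests within each arm have no control group, so any treatment given after baseline moves them directly.

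**Working it through.** **Inputs from the protocol.** 48 patients, 24 per arm; significance at P < 0.05 (two-sided assumed); unadjusted two-sample tests. The protocol gives no figure on drug use or drug effects, so there is nothing of its own to reproduce here.

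**Assumptions.** The protocol names no COVID-19 drug. Drug-use rates of 10-70%, drug effects of 0.5, 1.0 and 1.5 residual SD, and the IL-6 figures in step 5 are all assumed.

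**1. Reference effect size.** Detectable difference = (1.960 + 0.842) × √(2/24) = 0.81 SD at 80% power.

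**2. Chance imbalance.** Drug users per arm are taken as two independent Binomial(24, p) counts, summed exactly:

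| Assumed use p | P(difference ≥ 5 of 24) | P(difference ≥ 6 of 24) |
|---|---|---|
| 10% | 3.0% | 0.9% |
| 30% or 70% | 15.5% | 8.2% |
| 50% | 19.3% | 11.1% |

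A difference of 5 of 24 is 21 percentage points. It shifts the unadjusted mean difference by (5/24) × drug effect: 0.10, 0.21 or 0.31 residual SD for effects of 0.5, 1.0 or 1.5.

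**3. Error rate and power.** There were 40,000 simulated trials per row with no juice effect, comparing the t test with ANCOVA on drug use. Power is by normal approximation at a true juice effect of 0.81 residual SD. The unadjusted SD is √(1 + e²p(1−p)), where e is the drug effect. For example, p = 0.5 and e = 1.5 give √1.5625 = 1.25.

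| p | e | Type I error, unadjusted, all trials | Unadjusted, imbalance ≥ 5 | ANCOVA, all trials | ANCOVA, imbalance ≥ 5 | Power, unadjusted |
|---|---|---|---|---|---|---|
| 30% | 0.5 | 4.9% | 6.2% | 5.0% | 5.1% | 78% |
| 30% | 1.0 | 5.0% | 10.1% | 4.9% | 4.8% | 72% |
| 30% | 1.5 | 5.0% | 14.9% | 5.0% | 4.5% | 64% |
| 50% | 0.5 | 5.0% | 6.6% | 5.1% | 5.1% | 78% |
| 50% | 1.0 | 4.7% | 9.5% | 5.0% | 5.0% | 71% |
| 50% | 1.5 | 5.0% | 14.1% | 4.9% | 4.5% | 61% |

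With the covariate, power is about 80% in every row. That figure ignores the small cost of one degree of freedom and of any imbalance.

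**4. Within-group tests.** If a fraction p of an arm starts a drug with effect e after baseline, the arm's mean change moves by p × e whatever the juice does. At e = 1.0 that is 0.30 SD for p = 30% and 0.50 SD for p = 50%. Randomisation does not remove this, because the test does not compare arms.

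**5. IL-6 under a receptor blocker.** Assume that a blocker raises serum IL-6 tenfold in a fraction p of patients and that the log SD is otherwise 1.0. The variance of log IL-6 is then 1 + p(1−p)(ln 10)², with (ln 10)² = 5.30. The loss of information for a comparison of means on the log scale is 1 − 1/variance:

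- p = 5%: variance 1.25, loss 20%
- p = 10%: variance 1.48, loss 32%
- p = 15%: variance 1.68, loss 40%

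The penalty is smaller for Mann-Whitney: under the same assumptions it needs about 16%, 33% and 51% more patients, against 25%, 48% and 68% for the mean comparison.

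**The case against.** The strongest reply is that the trial is a "Randomized, Placebo-Controlled, Double-Blind, Parallel-Group clinical trial on patients with Covid-19". Chance differences in background drugs are part of what the 5% level covers, and an unadjusted comparison of randomised arms is valid. This stands, and the overall error rates in the working confirm it. A reader might infer that drug imbalance biases the between-group result or inflates its false-positive rate. The protocol does not support that: the 6-15% rates apply only within the subset of imbalanced trials.

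Second, covariates are often left to a statistical analysis plan, which is not shown. This stands in part. One cannot say that the drug records will never be used. One can say that the protocol names the tests, that those tests cannot use the records, and that this does not match the aim in its Follow up section.

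Third, corticosteroids and IL-6 blockers do not appear in the protocol. Their use at this hospital and their effects are assumptions. At 10% use, an imbalance of 5 patients is rare (3%).

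A reader might also infer that a few patients on an IL-6 blocker would dominate the IL-6 result. That is not shown. Under the tenfold assumption, two or three extra such patients in one arm shift mean log IL-6 by (2/24) × 2.30 = 0.19 to (3/24) × 2.30 = 0.29 residual SD. This is material but not overwhelming, and Mann-Whitney, which the protocol provides for, limits the influence of extreme values.

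**Conclusion.** The point holds as a mismatch between the stated aim and the fixed analysis, with a modest but real cost. It is not a flaw in the validity of the randomised comparison. Under assumed use of 30-50% and drug effects of 0.5-1.5 SD, the stated tests have 61-78% power where a covariate would give about 80%. In the 16-19% of trials with an imbalance of at least 5 of 24, the unadjusted false-positive rate is 6-15%, against 4.5-5.1% with the covariate. Lower use or weaker drug effects shrink both figures.

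The within-group tests are the more exposed part. A significant before-after change in the juice arm should not be read as an effect of the juice.

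**What to change.** In the Data analysis section:

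1. Compare the arms on each marker by regression (ANCOVA), on a log or rank scale if skewed. Include the baseline marker value and corticosteroid or other immunomodulator use at randomisation (yes/no) as covariates.
2. Report drugs started after randomisation by arm, and do not adjust for them, because the juice may influence their use. The baseline covariate will not remove the effect of such later drugs; the by-arm report lets the reader judge it.
3. If any patient is on an IL-6-receptor blocker at enrolment, repeat the IL-6 comparison without those patients as a sensitivity analysis. Do not exclude patients because a blocker was started after randomisation, since that selects on a post-randomisation event.
4. State that within-group changes are descriptive and that conclusions about the juice rest on the between-group comparison.

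The cost is one degree of freedom per covariate, one coded yes/no variable from records already planned, and a little more analysis work. No visit, sample or treatment changes.

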***Exclusion criteria***

- Transfer of patients to the intensive care unit

- Death
- Unwillingness to continue participating in the study

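### The protocol draws blood on the day a patient refuses to continue, makes no provision for that patient's week-2 sample, and does not settle whether or how the off-schedule value is analysed

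*Protocol*

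**What the plan says.** All of this is in the protocol.

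- **Clinical, Para clinical and dietary intake assessments.** The scheduled samples for CBC, CRP, ESR and IL-6 follow a fast ("10 cc blood samples will be obtained after 12 hour overnight fasting") and are taken "at the baseline and by the end of week-2". No other post-baseline sample is scheduled and no sampling window is given. Patients discharged early are followed up and kept on their assigned drink. For those who leave: "If the patient refuses to continue the study for any reason, blood sample will be drawn on the same day".
- **Data analysis.** "If the patient refuses to continue the study for any reason, statistical methods (Intention-to-treat analysis) will be performed". Groups are compared by independent t test or Mann-Whitney test, with paired t or Wilcoxon tests within groups. None has a term for sampling day.
- **Exclusion criteria.** The list includes "Unwillingness to continue participating in the study", beside transfer to intensive care and death.
- **Study Design & randomization.** There are 24 patients per arm, and "Patients will be followed for 14 days".

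**The concern.** The inflammatory markers and CBC are the primary objective, and the only scheduled post-baseline time is the end of week 2. A patient who refuses on, say, day 4 has one post-baseline value, from day 4. If it enters an unadjusted test beside day-14 values, the two arms may be compared at different average times. In patients hospitalised with Covid-19 these markers may well change over two weeks, so a difference in sampling time can look like a treatment effect. Unequal withdrawal is plausible: one arm drinks whole juice and the other coloured, flavoured water, 500 ml twice a day by the protocol's description. With 24 per arm, each patient is about 4% of an arm (1/24). The within-group paired tests would mix sampling days in the same way.

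The alternative reading, that refusers are excluded, avoids mixed sampling days but contradicts the intention-to-treat statement and removes patients for a reason arising after randomisation.

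**Working it through.** **No figure to reproduce.** The protocol states 48 patients without a power, SD, effect size or dropout rate. For scale only, with 24 per arm and two-sided alpha 0.05 (the protocol gives "P-Value <0.05 will be considered as statistically significant" and no sidedness), the detectable difference is (z for alpha + z for power) × √(2/24):

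- 80% power: (1.960 + 0.842) × 0.2887 = 0.81 SD
- 90% power: (1.960 + 1.282) × 0.2887 = 0.94 SD

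**Model, if the refusal-day value is used as the final value.** From the protocol: 24 per arm, 14 days, alpha 0.05. Assumed: no treatment effect; the marker falls linearly by *g* SD from day 0 to day 14, so a value from day *t* exceeds its day-14 level by *g*(1 − *t*/14) SD; *k* refusals per arm. Then

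bias (juice − placebo) = (k_J/24) × mean excess in juice − (k_P/24) × mean excess in placebo.

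With refusal days uniform over days 1 to 13, the mean day is 7 and the mean excess is 0.5*g*. For 2 versus 5, bias = (2 − 5)/24 × 0.5*g* = −0.0625*g*. Bias in SD follows, with simulated type I error in brackets (two-sided t test, 40,000 trials per cell, *k* fixed):

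| Refusals, juice / placebo | g = 0.5 | g = 1 | g = 2 | g = 3 |
|---|---|---|---|---|
| 2 / 5 | −0.03 (0.050) | −0.06 (0.052) | −0.13 (0.054) | −0.19 (0.058) |
| 1 / 6 | −0.05 (0.052) | −0.10 (0.061) | −0.21 (0.084) | −0.31 (0.121) |
| 2 / 10 | −0.08 (0.057) | −0.17 (0.081) | −0.33 (0.157) | −0.50 (0.254) |
| 4 / 4 | 0 (0.050) | 0 (0.046) | 0 (0.037) | 0 (0.026) |

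The sign reverses if the juice arm has more refusals, or if the marker rises over time. The last row shows the cost of balanced withdrawal: no bias, but added variance and a conservative test.

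**Number and timing act together.**

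- Equal numbers, different timing: 4 in juice at mean day 11.5 and 4 in placebo at mean day 2.5 give (4/24) × *g* × (2.5 − 11.5)/14 = −0.107*g*, that is −0.11, −0.21 and −0.32 SD for *g* = 1, 2, 3.
- Unequal numbers that cancel: 2 in juice at day 2 and 6 in placebo at day 10 give (2/24)(12/14)*g* − (6/24)(4/14)*g* = 0.

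**Ratio scale.** If a marker fell *F*-fold log-linearly, a day-*t* value would be F^((14−t)/14) times its day-14 value: 5^(7/14) = 2.24 for *F* = 5 at day 7, and 10^(11/14) = 6.11 for *F* = 10 at day 3. Three extra refusals in one arm shift its geometric mean by a factor of 2.24^(3/24) = 1.11 to 6.11^(3/24) = 1.25; two extra give 1.07 to 1.16. Without an SD on the log scale, this does not translate into an effect on the test.

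**If everyone is sampled at week 2**, this bias is 0 and the type I error is 0.05.

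**The case against.** The strongest reply is that the protocol orders a blood draw and gives it no role in the analysis. A reader might infer that last observation carried forward is prescribed. It is not: no sentence says the refusal-day value replaces week 2, intention-to-treat does not imply carrying a value forward, and the Exclusion criteria could mean these patients are dropped. Substitution is the natural reading only because this is the sole post-baseline value a refuser would have, the analysis is labelled intention-to-treat, and the tests ignore sampling day.

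Three other strong readings also go too far:

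- That early values are high. The protocol gives no time course, and CBC parameters need not start high or fall.
- That any imbalance in withdrawal creates an effect. The cancelling example above disproves this, and equal numbers can still bias.
- That a same-day draw cannot be fasting. A patient who refuses before breakfast could meet the 12-hour fast; the draw may miss it, no more.

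It is also fair to say that the missing-data method may sit in a statistical analysis plan not shown here, so its absence is not part of this point. What stands is the collection rule. Blood that was never drawn at week 2 cannot be recovered by a later analysis plan, and the conflict over whether refusers are analysed lies within the protocol itself.

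Finally, someone who leaves the study entirely may not agree to a later sample. That is true, and the exit draw is then worth having. But the protocol does not distinguish such a patient from one who only stops the drink.

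**Conclusion.** The point holds in conditional form. The protocol fixes an off-schedule draw for refusers, provides for no week-2 sample from them, and contradicts itself on whether they are analysed. Under one reading the comparison is open to bias from the number and timing of refusals; under the other it is not intention-to-treat.

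The likely size is modest. For 2 versus 5 refusals, the worst case examined (0.19 SD) is under a quarter of the 0.81 SD detectable at 80% power (0.19/0.81 = 0.23), and type I error stays at or below 0.058. It becomes serious only with a large imbalance and a steep decline: 0.50 SD is 0.62 of the detectable difference, with type I error 0.25. These figures rest on assumed declines, refusal counts and refusal days, and were simulated for the t test only.

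The point covers refusals alone. Discharged patients are already followed, and no corresponding draw is ordered for intensive-care transfer or death. It should be corrected because the remedy is cheap and must be in place before samples are lost.

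**What to change.** 1. Distinguish stopping the assigned drink from leaving follow-up. This concerns data collection only and changes no treatment rule.
2. Seek the fasting week-2 sample from every randomised patient who still consents to sampling, building on the follow-up already planned after discharge.
3. Record the actual day and fasting state of every sample.
4. Keep the refusal-day sample as a dated extra observation, and state that it is not a week-2 value.
5. Where week 2 is missing, use a method that accounts for sampling day, such as a mixed model on all dated samples, or multiple imputation, with a sensitivity analysis. This can go in the statistical analysis plan.
6. Reconcile the Exclusion criteria, the assessments section and Data analysis, so that one rule says whether patients who refuse are analysed.

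The cost is a protocol wording change, one already planned type of sample for the few who stop, and slightly more analysis. Some patients will decline the later sample, so the fix reduces the problem but may not remove it.

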### **Follow up:**

Subsequent follow-up is to detect and minimize the effects of the confounding factors, as well as to accurately carry out the intervention protocol and will be done by well-trained, committed researchers.

## **Study objectives:**

### ***Primary objectives***

To assess of the effect of Punica granatum juice on inflammatory biomarkers and CBC in patients with Covid-19

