### ***Secondary objectives***

- To assess and compare the mean or median serum concentrations of interleukin 6 before and after the intervention and between the intervention group with placebo
- To assess and compare the mean or median serum concentrations of ESR before and after the intervention and between the intervention group with placebo
- To assess and compare the mean or median serum concentrations of CRP before and after the intervention and between the intervention group with placebo
- To assess and compare the mean or median of CBC parameters before and after the intervention and between the intervention group with placebo

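### The protocol names no single primary endpoint: the primary objective is the whole panel of inflammatory markers and blood count, and the secondary objectives list the same variables again

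*Protocol*

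**What the plan says.** Under Primary objectives the protocol has a single sentence: "To assess of the effect of Punica granatum juice on inflammatory biomarkers and CBC in patients with Covid-19". The assessments section shows what that covers. Blood is drawn for "complete blood count (CBC) and inflammatory indices including CRP, ESR & IL-6, at the baseline and by the end of week-2", so there are at least three inflammatory markers plus a full blood count. The CBC parameters are neither listed nor counted.

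Under Secondary objectives there are four items, one each for IL-6, ESR, CRP and the CBC. The first reads "To assess and compare the mean or median serum concentrations of interleukin 6 before and after the intervention and between the intervention group with placebo" and the last asks to "compare the mean or median of CBC parameters before and after the intervention and between the intervention group with placebo". Together they cover the same variables as the primary objective and add no others.

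Data analysis gives the tests and the threshold. Between groups: "Independent T Test and Mann Whitney test will be used to compare the mean of variables between two groups". Within groups: "Paired T test or Wilcoxon test will be used to analyses within groups means". For all of them: "P-Value <0.05 will be considered as statistically significant". No section ranks the variables or says how several results combine into an answer to the primary objective.

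**The concern.** A primary endpoint fixes in advance which result answers the trial's question and at what error rate. Here the primary tier is an open-ended panel and the secondary tier is the same panel itemised, so the labels separate nothing. A reader of the final report could not tell from the protocol whether a significant ESR beside flat CRP and IL-6 supports the primary claim, fails to support it, or is incidental.

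With one unadjusted threshold across the panel, the chance that at least one marker differs between groups by luck is well above 5%. In a trial with 24 patients per arm, an isolated significant marker is a plausible outcome of an ineffective drink, and nothing in the protocol would prevent it from carrying the main conclusion.

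**Working it through.** The protocol gives no family-wise error rate, power or effect size, so there is no stated figure to reproduce beyond the 0.05 threshold.

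**Inputs**
- Threshold per test: α = 0.05 (Data analysis). Sidedness is not stated; two-sided is assumed.
- Patients: 48, 24 per arm (Study Design & randomization).
- Named inflammatory markers: 3, namely CRP, ESR and IL-6 (assessments section).
- CBC parameters: number not given. *Assumed* 5 to 8, so k = 3 + 5 = 8 to 3 + 8 = 11 between-group tests.
- Correlation between markers: not given. *Assumed* values 0, 0.5 and 0.8, equal for all pairs.

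**Step 1. Independent tests, no effect of the juice.** Chance of at least one P<0.05 = 1 − 0.95^k.
- k = 3: 1 − 0.857 = 14.3%
- k = 8: 1 − 0.663 = 33.7%
- k = 11: 1 − 0.569 = 43.1%

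**Step 2. Correlated tests.** Simulation of 24 versus 24 patients with equicorrelated normal outcomes, no group difference, two-sided t tests at 0.05 and 200,000 runs per setting (Monte Carlo standard error about 0.1 percentage point).

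| k | correlation 0 | 0.5 | 0.8 |
|---|---|---|---|
| 3 (named markers only) | 14.1% | 12.6% | 9.8% |
| 8 | 33.7% | 25.1% | 16.0% |
| 11 | 43.2% | 30.9% | 18.2% |

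The zero-correlation column agrees with Step 1. The lowest figure, three markers correlated at 0.8, is still about twice the nominal 5%.

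**Step 3. Which remedy 48 patients can afford.** Approximate power for a standardised difference d with n per arm is Φ(d·√(n/2) − z), where z is the two-sided critical value. With d = 0.8 and n = 24, d·√12 = 2.771.
- One primary variable at 0.05: Φ(2.771 − 1.960) = Φ(0.811) = 79%.
- Bonferroni over an assumed 10 tests, 0.05/10 = 0.005 each: Φ(2.771 − 2.807) = Φ(−0.036) = 49%.

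The exact t-based values are slightly lower (77% and 44%), with the same message. The value 0.8 SD is illustrative, since the protocol gives no target difference. Naming one variable holds the error of the main claim at 5% without this loss.

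Within-group tests are left out of the count. Markers in hospitalised patients can change over 14 days as they recover, so a significant paired test on an inert drink may reflect a real change over time and is not necessarily a type I error.

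**The case against.** The strongest reply is that the statistical analysis plan is not shown, and multiplicity methods and testing hierarchies are commonly left to it. That stands as far as it goes: the lack of an adjustment method in the protocol is not the point, and one cannot say that the trial has no type I error control, only that this document states none. Choosing the primary endpoint is different. It is a protocol decision, and here it has been made badly, by declaring a whole panel primary and repeating it as secondary. A later correction would not show which variable the trial was meant to answer.

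Some stronger readings are tempting but not supported:
- *Any one significant marker counts as success.* The protocol has no success rule. The objectives only assess and compare. The text leaves this reading open without stating it.
- *No result could refute the claim.* A trial with no significant marker would not support it. The fault is an undefined claim with an inflated error rate, not an unfalsifiable one.
- *A false-positive finding is likely.* Every figure under the stated assumptions is below one half.
- *There are about ten tests.* The number of CBC parameters is assumed. The conclusion survives because the three named markers alone already exceed 5%.

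It is also fair to say that CRP is not the only defensible primary variable. The background mentions lowering CRP, but it also discusses cytokine excess, which could motivate IL-6.

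**Conclusion.** The point holds in this form: the protocol does not identify a primary endpoint, its primary and secondary objectives cover the same variables, and one P<0.05 threshold applies throughout with no statement of what would support the primary claim.

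Followed as written, the chance of at least one spurious between-group difference is about two to three times nominal on the named markers alone. With the assumed CBC panel it is roughly three to nine times nominal (16% to 43%). The size rests on the assumed number of CBC parameters and the assumed correlation; the direction does not. The defect in the objectives can be read directly from the text and depends on neither assumption.

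**What to change.** Rewrite the primary objective to name one variable, the between-group contrast and the time point, and fix it before unblinding. An example is CRP at the end of week 2, juice versus placebo, two-sided 0.05. The sponsor may justify another marker such as IL-6, or co-primary variables with a stated split of alpha. The wording should also say what value stands for week 2 in patients who leave early, since the assessments section takes their blood on the day they refuse to continue.

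Make the remaining inflammatory markers secondary with a Holm correction, and remove the primary variable from the secondary list. List the CBC parameters and report them as exploratory, with confidence intervals and no claim of significance.

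The cost is more than editing. The protocol describes itself as ethics-approved and registered, so this needs a protocol and registry amendment. The scientific price is that a significant result on another marker can no longer carry the main conclusion. No extra patients or measurements are needed.
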